# Mobile rehabilitation support versus usual care in patients after total hip or knee arthroplasty: study protocol for a randomised controlled trial

**DOI:** 10.1186/s13063-022-06269-x

**Published:** 2022-07-08

**Keywords:** Telerehabilitation, Mobile application, Total hip arthroplasty, Total knee arthroplasty, Self-efficacy, Physical function, Pain, Depression, Anxiety, Health-related quality of life

## Abstract

**Background:**

The global increase in total hip or knee arthroplasty has led to concern about the provision of postoperative rehabilitation. Telerehabilitation may be a strategy to meet the patients’ requirements for rehabilitation after arthroplasty. This study aims to investigate the effectiveness of a telerehabilitation programme delivered via the mobile application WeChat in patients after total hip or knee arthroplasty on the following outcomes: self-efficacy, physical function, pain, depression, anxiety and health-related quality of life.

**Methods:**

This is a single-centre, single-blinded, parallel-group, superiority randomised controlled trial conducted in Shanghai, China. Eighty-four eligible participants who undergo primary total hip or knee arthroplasty will be recruited preoperatively in a university teaching hospital and randomly assigned to the experimental or control group with their informed consent. Once discharged, the control group (*n* = 42) will receive the usual care provided by the hospital. The experimental group (*n* = 42) will receive usual care and a 6-week mobile application rehabilitation programme that consists of physical exercises and techniques for enhancing participants’ self-efficacy for rehabilitation. Baseline assessments will be conducted on the day before hospital discharge, and outcome assessments will be conducted 6 and 10 weeks postoperatively. The primary outcomes are changes in self-efficacy and physical function 6 weeks postoperatively, and the secondary outcomes include pain, depression, anxiety and health-related quality of life. The approach of a generalised estimating equation will be used to analyse the effect of the intervention on outcomes at a significance level of 0.05.

**Discussion:**

This study is the first of its kind conducted in China to incorporate self-efficacy and learning theories as a framework to guide the development of a mobile application rehabilitation programme after arthroplasty. This study will contribute to the knowledge about the effectiveness of mobile application-based rehabilitation among patients after total hip or knee arthroplasty. If the findings are positive, they will support the implementation of mobile application-based rehabilitation in practice, which may potentially increase the accessibility of rehabilitation services as well as patient adherence to rehabilitation.

**Trial registration:**

Australian New Zealand Clinical Trials Registry ACTRN12621000867897. Retrospectively registered on July 6, 2021

**Supplementary Information:**

The online version contains supplementary material available at 10.1186/s13063-022-06269-x.

## Background

Total hip arthroplasty (THA) and total knee arthroplasty (TKA) are two common surgical procedures to treat end-stage degenerative osteoarthritis [1, 2] and primarily occur in older populations [3]. With the ageing population and the increased prevalence of osteoarthritis, the number of THA and TKA procedures has risen globally [4]. Over three million THA and TKA procedures were performed in 2017 around the world [5], which is an increase of 40% compared to the number in 2007 [6, 7]. The involvement of patients in postoperative rehabilitation is important to promote recovery, relieve pain, enhance muscle strength, optimise physical function and improve health-related quality of life (HRQoL) [8, 9].

Rehabilitation services for patients after THA or TKA are conventionally provided face to face at inpatient rehabilitation units or outpatient rehabilitation departments [10, 11]. For people who live in remote areas with limited local health care resources or during a pandemic, such as COVID-19, access to face-to-face rehabilitation services may be difficult [12, 13]. The rapidly growing demand for rehabilitation also challenges the sustainability of face-to-face rehabilitation services [14]. With the advancement in technology, telerehabilitation, which refers to the remote delivery of rehabilitation services via information and communication technologies, such as telephones and computers, has emerged to complement or offer an alternative to face-to-face rehabilitation [15, 16]. Among all these telerehabilitation services, mobile applications (apps) are increasingly being used because they are easy to access [17] and allow health care professionals to provide support whenever and wherever patients need it [18, 19].

The effectiveness of mobile app-based rehabilitation among patients after THA or TKA has been evaluated by several studies conducted in the USA, Australia, Portugal and China [18, 20–25]. These studies delivered rehabilitation services, such as exercise demonstrations, reminders, progress monitoring and follow-up, via mobile apps to the patients at home. These studies supported that mobile app-based rehabilitation, when compared to face-to-face rehabilitation, had the potential to achieve similar outcomes in pain relief as well as in the improvement of physical function, range of motion and HRQoL. However, these studies, except two [18, 25], were quasi-experimental or cohort studies. Evidence derived from randomised controlled trials (RCTs) is essential, as RCTs are considered the gold standard to investigate the effectiveness of interventions [26].

Psychological outcomes were seldom measured in previous studies [27]. Many patients after hip or knee arthroplasty experience psychological problems, such as depression and anxiety [28]. These problems negatively impacted their postoperative outcomes, such as experiencing more pain, lower physical function and higher dissatisfaction [29, 30]. Patients’ self-efficacy is also a critical psychological factor that impacts patients’ motivation, adherence and performance in rehabilitation [31], which would further influence their postoperative physical function and psychological well-being [32]. Thus, in addition to the outcomes that were commonly assessed in previous studies (i.e., pain, physical function, range of motion and HRQoL), psychological outcomes regarding depression, anxiety and self-efficacy should be included in the evaluation of the effectiveness of mobile app-based rehabilitation [11, 32, 33]. Furthermore, the application of a theoretical framework was seldom reported in the development of existing mobile app programmes, which may affect the programmes’ quality and utility [34, 35].

In China, approximately 689,000 THA or TKA procedures are performed annually [36]. The accessibility of face-to-face postoperative rehabilitation services is insufficient, mainly due to the lack of rehabilitation facilities and qualified health care professionals [37, 38]. Therefore, the rehabilitation programmes in some Chinese hospitals consist of written and pictorial instructions provided to the patients at hospital discharge that the patients follow at home instead of attending the clinic for face-to-face rehabilitation [23]. However, patient adherence to this type of  rehabilitation 3 months after surgery was only 23.5% (*n* = 213) because patients did not have support from health care professionals [39]. The wide uptake of smartphones in China has led health care professionals to support patient care at home via mobile apps such as WeChat [23, 24]. Current mobile app programmes mainly focus on diabetes, hypertension and hepatitis [40], whereas those targeting arthroplasty are lacking [41]. Thus, rigorously controlled trials with theory-based interventions are warranted to support evidence-based practice in mobile app-based rehabilitation among Chinese patients after THA or TKA.

This study aims to evaluate the effectiveness of a mobile app rehabilitation programme compared with usual care among Chinese patients after THA or TKA regarding the outcomes of self-efficacy, physical function, pain, depression, anxiety and HRQoL. We hypothesise that compared to the control group receiving usual care, the experimental group receiving the mobile app rehabilitation programme in addition to usual care will report a significant improvement in self-efficacy, physical function and HRQoL as well as a significant reduction in pain, depression and anxiety.

## Methods/design

### Study design

This is a single-centre, single-blinded, superiority RCT with two parallel groups. Participants undergoing primary THA or TKA will be recruited preoperatively in the orthopaedic wards. They will receive standard inpatient rehabilitation services and the same care during hospitalisation. On the day before hospital discharge, they will complete the baseline assessment (T0) and will be randomly assigned to the experimental or control group. Once discharged, the experimental group will receive a 6-week mobile app rehabilitation programme and usual care, whereas the control group will receive usual care for 6 weeks. Outcomes will be assessed at 6 weeks (T1) and 10 weeks (T2) after hospital discharge. The flowchart of the RCT is presented in Fig. 1. The Standard Protocol Items: Recommendations for Interventional Trials (SPIRIT) checklist is provided in Additional file 1.

**Fig. 1 Fig1:**
[figure not shown]
Flow chart of the trial

#### Sample size

The sample size was calculated using the formula developed by Sugimoto et al. [42], incorporating the co-primary outcomes of this study: physical function and self-efficacy. Based on previous studies in arthroplasty, we expect the effect size of the intervention on self-efficacy to be 1.2 and that on the physical function to be 0.7 [20, 43]. The effect size ratio is approximately 1.7 (1.2/0.7). The correlation coefficient between these two outcomes was estimated to be 0.3 [44]. We set the attrition or nonresponse rate at 20% based on the evidence from the study of Walters et al. [45]. The present study requires a sample size of 84 in all (42 in each group) to achieve a power of 0.8 at a 0.025 level of alpha error.

#### Randomisation

Participants will be randomly assigned to the experimental or control group using simple randomisation with a 1:1 allocation ratio. A person who is not a member of the research team produced the allocation sets using a computerised random number generator. The allocation sequence will be concealed from the researchers using enclosed identical, sequentially numbered, opaque, sealed envelopes, which are impermeable to intense light. After a participant has been enrolled and has completed the baseline assessment, the researcher (QW) will open the next sealed envelope and assign the participant to the indicated group.

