#### Inclusion criteria

The inclusion criteria are (1) adults (greater than or equal to 18 years) after unilateral primary THA or TKA, (2) possess a mobile device (e.g., smartphone or tablet) with an Internet connection, (3) able to access the mobile app WeChat, (4) able to complete the programme and relevant follow-up 3 months after hospital discharge, (5) able to communicate with the researcher in Chinese (Mandarin) and (6) able to provide informed valid consent to participate in the study.

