#### Primary outcomes

The primary outcomes are changes from baseline in self-efficacy and physical function at the completion of the intervention (T1). The intervention is based on the self-efficacy theory, aiming to improve patients’ physical function after surgery. These two outcomes may provide the most relevant and convincing evidence related to the aim of this study. The study results will be considered positive only if the intervention has an effect on both primary outcomes; thus, no adjustment for multiplicity will be conducted in data analysis [56].

Patients’ self-efficacy for rehabilitation will be measured using the Chinese version of the Self-Efficacy for Rehabilitation Outcome Scale (SER) [57]. The SER is sufficiently reliable and valid to detect patients’ self-efficacy for rehabilitation after hip or knee reconstructive/replacement surgeries [58]. It consists of 12 items that assess individuals’ beliefs in their ability to perform behaviours typical of physical rehabilitation, and each item is rated on an 11-point Likert scale from 0 indicating ‘I cannot do it’ to 10 indicating ‘certain I can do it’ [59]. Higher scores indicate greater self-efficacy.

Patients’ physical function will be measured using the Chinese version of the Hip Disability and Osteoarthritis Outcome Score Physical Function Short Form (HOOS-PS) for patients after THA and the Knee Injury and Osteoarthritis Outcome Score Physical Function Short Form (KOOS-PS) for patients after TKA [60, 61]. The HOOS-PS and KOOS-PS are valid for assessing patients’ perceptions of their hip or knee functions [62]. The HOOS-PS has five items, whereas the KOOS-PS has seven. Each item is graded from 0 indicating ‘no difficulty’ to 4 indicating ‘extreme difficulty’ [60, 61]. The raw sum score can be further converted in two directions: from no difficulty (0) to extreme difficulty (100) or from extreme difficulty (0) to no difficulty (100) [63]. To align with other scales in this study, such as the SER and EQ-5D-5L, the scores will be summed using the nomogram of worst (0) to best (100), with higher scores indicating better physical function. The minimal clinically important difference used in this study is 8 points for the HOOS-PS or KOOS-PS [64].

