### Data analysis plan

IBM® SPSS Statistics 26.0 will be used to analyse the data [72]. The first author will perform data entry and analysis using participants’ identification codes. Categorical variables, such as gender, will be presented in frequencies and percentages. Continuous variables, such as age, will be presented as means with standard deviations or medians with interquartile ranges. Demographic characteristics and baseline variables will be compared between the two groups. Student’s *t*-tests will be used if the continuous data are normally distributed; otherwise, Wilcoxon rank-sum tests will be used. For categorical data, chi-square tests or Fisher exact tests will be conducted when chi-square testing is not valid. The effectiveness of the intervention will be analysed using the intention-to-treat principle [73]. The generalised estimating equation (GEE) model [74] will be used to compare the differential changes in the outcome variables between the groups across time points at a significance level of 0.05 (two-tailed). The GEE increases the efficiency of the estimates of the parameters in longitudinal trials by accounting for the within-subject correlations in repeated measurements [75]. This model is flexible to use as it relaxes the distribution assumptions of observed data and can accommodate missing data due to dropouts in RCTs [75, 76]. No imputation will be conducted if the proportion of missing data is less than 5% as the GEE can naturally integrate the missing data; otherwise, multiple imputations may be conducted [77].

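### Physical function pools hip and knee patients on two instruments with no joint term in the stated model; adding one would gain precision, not remove a bias

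*Protocol article*

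**What the plan says.** The trial enrols "adults (greater than or equal to 18 years) after unilateral primary THA or TKA" (Inclusion criteria). No hip/knee split is expected or enforced. Allocation is unrestricted: "Participants will be randomly assigned to the experimental or control group using simple randomisation with a 1:1 allocation ratio" (Randomisation).

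Physical function is one of two co-primary outcomes, each defined as change from baseline to T1. Hip patients answer the HOOS-PS and knee patients the KOOS-PS: "The HOOS-PS has five items, whereas the KOOS-PS has seven" (Primary outcomes). Both are converted to 0–100, with higher scores better, and share one threshold: "The minimal clinically important difference used in this study is 8 points for the HOOS-PS or KOOS-PS". The Sample size section uses a single physical-function effect size of 0.7. The outcome is therefore treated as one variable across joints.

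Success is conjunctive: "The study results will be considered positive only if the intervention has an effect on both primary outcomes".

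The Data analysis plan describes a GEE that compares change between groups over time, and it names no covariate. On baseline differences it says only this: "Demographic characteristics and baseline variables will be compared between the two groups".

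**The concern.** Joint determines the operation and the questionnaire, and it is known for every patient before allocation. It is used neither in the allocation nor, as far as the article goes, in the model. If hip and knee patients differ in how much their converted score changes by T1, that difference adds to the residual spread of a co-primary outcome. Comparing baseline variables between arms may reveal an uneven hip/knee mix but does nothing about it.

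Precision on physical function matters because it carries the smaller planned effect (0.7 against 1.2 for self-efficacy) and the trial must succeed on both. Avoidable noise here feeds almost directly into the power of the whole trial.

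**Working it through.** **Inputs from the article.** Effect sizes 1.2 (self-efficacy) and 0.7 (physical function), correlation 0.3, attrition 20%, power 0.8, alpha 0.025 (Sample size); two-tailed 0.05 tests (Data analysis plan).

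**Assumptions, because the article gives no figure.** Hip share h = 0.5, with 0.3 as a check. Between-joint difference in change, g, from 0 to 1.0 within-joint SD. The 0.7 is first taken to be in within-joint SD units.

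**1. The planned sample size.** Power to win on both outcomes with n evaluable per group is the bivariate normal probability

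Φ₂(1.2√(n/2) − 1.96, 0.7√(n/2) − 1.96; ρ = 0.3).

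Reading 0.025 as one-sided, which matches a two-sided 0.05 test, n = 33 is the first to reach 0.8 (power 0.811). Then 33/0.8 = 41.25, rounded up to 42 per group, or 84 in all. The stated figure reproduces. The expected number evaluable is 42 × 0.8 = 33.6, taken as 34 per group below, where power is 0.822.

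**2. Leaving joint out.** The variance of the pooled change score is 1 + h(1 − h)g² and the working effect size is 0.7/√(1 + h(1 − h)g²). For h = 0.5 and g = 0.5: 1 + 0.25 × 0.25 = 1.0625, and 0.7/1.031 = 0.679.

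| g (SD) | Variance, h = 0.5 | Effect size, h = 0.5 | Power on both, h = 0.5 | Power on both, h = 0.3 |
|---|---|---|---|---|
| 0 | 1.000 | 0.700 | 0.822 | 0.822 |
| 0.25 | 1.016 | 0.695 | 0.816 | 0.817 |
| 0.5 | 1.063 | 0.679 | 0.799 | 0.803 |
| 0.75 | 1.141 | 0.655 | 0.771 | 0.779 |
| 1.0 | 1.250 | 0.626 | 0.732 | 0.746 |

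**3. Chance imbalance is the same quantity, not a second harm.** With 34 per arm and h = 0.5, the between-arm difference in hip share has SD √(2 × 0.25/34) = 0.121. At g = 0.5 the resulting shift in the effect has SD 0.121 × 0.5 = 0.061, so its variance is 0.0037. The extra variance from step 2 is (2/34) × 0.0625 = 0.0037. These are one component, and the unadjusted standard error, √(0.0588 + 0.0037) = 0.25, already contains it.

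**4. Type I error.** In 40,000 simulated null trials per setting (68 patients, half hips, simple randomisation, unadjusted two-sided t-test at 0.05), the rejection rate was 0.052, 0.051 and 0.051 for g = 0, 0.5 and 1.0.

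**5. If 0.7 came from a mixed-joint sample.** Its SD then already includes the between-joint part, and 84 is adequate unadjusted. Adjustment would raise the working effect size to 0.7 × √1.0625 = 0.72 at g = 0.5, or 0.7 × √1.25 = 0.78 at g = 1.0.

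**The case against.** The strongest reply is that the missing joint term is inferred from silence. The article does not say that the GEE is unadjusted, and an analysis plan that is not shown may list covariates. That stands as a limit: the article cannot be charged with ruling adjustment out. It does not dispose of the suggestion, because the model as described has no joint term and adding one is concrete and nearly free.

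Second, the outcome is change from baseline, so a constant level difference between hips and knees cancels. This also stands. Only a difference in recovery or in scale metric matters, and the article gives no evidence of its size. Unequal item counts do not by themselves make the two converted scores incomparable.

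Third, a reader might infer that an uneven hip/knee mix confounds the result. In a single trial it can shift the estimate. With 84 randomised and half hips, the hip share differs by at least 20 points with probability 0.07, and at g = 0.5 that moves the estimate by 0.2 × 0.5 = 0.10 SD, or 14% of 0.7. But the shift averages to zero over randomisations and the unadjusted interval allows for it.

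Fourth, a reader might infer that the list should be stratified. The documents do not support this as a requirement. The unblinded researcher who recruits also opens the envelopes and delivers the intervention, and stratified blocks are more predictable than simple randomisation. The Trial status section also reports 48 already recruited, with completion expected in October 2021.

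Fifth, simple randomisation gives exactly 42:42 with probability of only 8.7%, which might look like a contradiction of the planned group size. The 42 reads as a planning figure, and the cost is trivial: a 47:37 split has an effective size of 4 × 47 × 37/84 = 82.8, a loss of 1.4%.

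**Conclusion.** The point holds as a matter of precision. A co-primary outcome pools two joints on two instruments, allocation ignores joint, and the model as described has no term for it. There is no systematic bias and no inflation of type I error, and the documents do not show that the pooled score is invalid or that the allocation method is wrong.

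The size depends on two unstated quantities. With half hips and 0.7 in within-joint units, the loss is negligible at a between-joint difference in change of 0.25 SD, about two power points at 0.5 SD (variance up 6%) and about nine at 1.0 SD. With 30% hips it is slightly smaller. If 0.7 already reflects a mixed sample, the planned power is intact and adjustment only adds to it.

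**What to change.** Prespecify joint (THA/TKA) and joint-by-time as covariates in the primary GEE for each outcome, before outcome data by group are examined. The interaction is needed where baseline is one of the modelled time points: a joint main effect alone absorbs only a constant level difference, which already cancels in the change. Report the physical-function effect separately for HOOS-PS and KOOS-PS patients as a description, without subgroup claims.

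The cost is analysis wording and one degree of freedom in a T1 change-score comparison, two (joint, joint-by-time) if T1 and T2 are the responses, or three if T0 is a response as well. Joint is already known for every patient, since it decides which questionnaire is given. The sample size of 84 and the randomisation list need no change.

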#### Blinding

Due to the nature of the intervention, the experimental group will use a mobile app while the control group will not; it is impossible to blind the participants and the researcher (QW) who will deliver the intervention. However, the outcome assessor, a research assistant who has no relationship with the participants, will be blinded to the allocations throughout the study. The researcher (QW) will provide the assessor with assessment training prior to the study. The assessor will independently assess all outcomes for the two groups at T0, T1 and T2. Participants are required in advance not to communicate with the assessor about to which group they are allocated.

